## V. STUDY PROCEDURES

Participants will be randomized 1:1 to 3RP-NF or HLI using a permuted-block randomization, stratified by diagnosis. Stratification ensures that an equal number of participants with NF1, NF2 and schwannomatosis are allocated to both treatments. Randomization will be generated by a computer.

We will use the same clinician/study therapist across the study conditions. Consideration was given to using different therapists for each arm to minimize potential contamination. However, observed study effects might be then attributable to clinician/therapist factors, and the study manuals are distinct. To deal with potential contamination, we will employ the audio-recording supervision and review as detailed below, including the use of checklists to document therapist fidelity to the intervention and also to prevent drift.

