**1.1. Experimental treatment: The Relaxation Response Resiliency Program for patients with NF (3RP-NF).** The original 3RP program manual was modified to address specific needs of patients with NF, which were identified previously during 2 focus groups (N = 15 participants) and literature review. During these focus groups patients were asked open ended questions about the need for a mind body group, interest in potential participation, difficulties managing NF, and about specific stressors associated with NF1, NF2 and schwannomatosis. Specific modifications included: 1) specific skills aimed at managing NF specific stressors such as burden of medical appointments, dating and difficulties hearing; 2) restructuring NF specific thoughts such as those associated with self image, career, etc; and 3) learning acceptance techniques to address issues associated with making sense of having NF and dealing with the uncertainty of having this condition. The original 3RP manual was modified to address these changes and was used uniformly with each group. Each of the 8 sessions involves a review of previously learned skills, introducing and practicing a new relaxation response technique, and learning a specific cognitive behavioral or positive psychology based skills and applying it to specific patient specific issues. Participants receive 2 relaxation CDs to ease practice at home, as well as a patient manual. Participants are instructed in the importance of practicing the skills at home, and homework forms are collected at the beginning of each session. Further, every session includes discussions on homework completion and problem solving barriers to practice. Groups are small (5-7 participants/group) allowing the facilitator to ensure that patients understand and practice the skills taught. The 3 diagnostic categories are grouped together for the purpose of this study for several reasons. First, there are many similarities among patients with NF1, NF2 and schwannomatosis such as common stressors associated with symptoms (e.g., appearance concerns, pain, uncertainty about progression/growth of tumors, social isolations, concerns about transmission through pregnancy). Second, patients within the 3 categories, as a group, share similar psychosocial difficulties and decreased quality of life. Third, the 3RP is not aimed to target underlying diseases processes, as would a drug; rather, it is aimed at improving coping with stress and symptoms (e.g., increase resiliency) and satisfaction with life. We deal with the heterogeneity of NF by asking patients to set general and weekly practice goals that are specific to them, and teaching them to apply them to their individual goals and concerns. For example, a patient with NF1 who has facial tumors might set a goal of decreasing self-consciousness while a patient with schwannomatosis might set a goal of improving coping with pain. Both patients can benefit from relaxation response strategies as well as from cognitive behavioral and positive psychology skills to help them develop acceptance and an adaptive response to a chronic incurable condition. Lastly, this decision is based on preliminary research. We found no differences in baseline characteristics of patients with NF1, NF2 and schwannomatosis on any of the study variables, with the exception of pain intensity, which was the highest in patients with schwannomatosis. Further, research on the 3RP has shown that patients with various medical and psychiatric concerns respond similarly to the mind body intervention (Gonzalez, [name], & Park, submitted).

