## MIND-BODY SKILLS TRAINING FOR ADULTS WITH NEUROFIBROMATOSIS

represents the basis of this research. Such control interventions are routinely used in stringent RCTs of psychosocial interventions. The HEP-NF program consists on 8 group sessions (each session is 90 minutes) that occur concurrently with the active intervention condition 3RP-NF. The active comparison HEP-NF is conducted in the same format as the intervention condition but does not include any relaxation response, cognitive behavioral or positive psychology skills training that are reflected in the 3RP-NF. Patients in the HEP-NF receive the same attention from the study therapist as those in the 3RP-NF.

**6. Protocol integrity.** The integrity of the 3RP-NF and HEP-NF protocols will be assured empirically. All sessions will be audiotaped. We have developed a rating checklist for therapist adherence that includes whether the specific components of each session was in fact delivered. Adherence ratings will be completed by [name]. Competence will be ensured by weekly clinical supervision using audiotapes. At least 20% of the sessions, and at least one session per week, will be reviewed prior to clinical supervision meetings, and the rating checklist will be used to give specific feedback to study therapists.

**7. Strategies to avoid participant unblinding:** Participants will not know whether they are assigned to the 3RP-NF intervention or the HEP-NF control. Rather, they will be informed that they will be randomized to one of 2 stress management groups, in an effort to identify which one works best in patients with NF. In order to prevent unblinding, participants will be asked to not share information discussed in the group on social media sites (e.g., Facebook groups or internet chat groups) or with other NF acquaintances for the duration of the study. We will also explain to study participants how sharing of information would potentially negatively impact the validity of study results. It is important to mention that we have evidence that the HEP-NF control is credible and patients remained generally blind, as we found no differences in scores of satisfaction with overall program at posttest or 6 month follow up. Nevertheless, we anticipate some level of disclosure of techniques from the 3RP-NF groups to the HEP-NF control groups via social media sites, which would make our findings conservative by potentially *underestimating* the true efficacy.

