post-intervention) and durability (to 6 and 12 months) of the 3RP-NF. Accordingly, the primary analysis will compare changes in primary and secondary outcomes (continuous measures) from baseline to the post-, 6 months and 12 months visits between the randomized conditions. All randomized participants will be included in our primary efficacy analyses as randomized, following the intention-to-treat principle. Data will be analyzed using a shared-baseline, linear mixed model with fully unstructured covariance among repeated measures. The shared-baseline assumption reflects the true state of the population prior to randomization and has the benefit of adjusting for chance differences at baseline. For each outcome, we will compare the effect of 3RP-NF vs. HEP-NF on changes from baseline to the post-test, 6 and 12 months follow-up times using linear contrasts. Our primary aim will focus on the post-treatment follow-up time. With two co-primary outcomes, we will use two-sided tests at  $p < 0.025$  to declare superiority of 3RP-NF, maintaining an overall 5% type 1 error at our primary post-intervention time point. Persistence of a benefit from 3RP-NF at 6 and 12 month follow-up times will be analyzed as a non-inferiority test of durability. Non-inferiority of 3RP-NF in maintaining benefits relative to HEP-NF will be declared if the lower one-sided 95% confidence bound for a given co-primary outcome is less than 6.25 units (the estimated MCID) in favor of HEP-NF. Several sensitivity analyses will be explored using alternative models. Change scores at post-intervention, 6 months, and 12 months will be separately analyzed by Wilcoxon rank sum test to avoid any parametric assumptions about the data. More parsimonious covariance structures will be considered using random participant-specific intercepts, slopes, and quadratic terms (i.e., growth curve analysis). Baseline parameters such as NRS pain will be included to account for chance differences due to randomization and to explain sources of variation in response that are independent of treatment group.

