While no information on clinically meaningful differences exists for the primary outcome measures for patients with NF, we will also use both “distribution-based” and “anchor-based” methods as criteria to determine important change. Consistent with “anchor based” methods, we will ask patients at post-treatment, 6 and 12 months follow ups to rate whether they were “substantially better”, “minimally better” “about the same”, “minimally worse” or “substantially worse” as compared to how they were before the intervention. These improvement ratings would thus serve as the standard with which to evaluate the importance to the patient of whatever changes in quality of life occurred during the intervention. Success of the trial will thus be estimated based on outcome score (quality of life scores) and anchor-based measures of subjective improvement. The anchor-based MCID estimates will be computed using prior methodology, as the mean change in the physical health and psychological health QoL among those in the “minimally better” category.

**3.1. Power Consideration and Sample Size Calculations.** The effective standard deviation (SD) for the change from baseline to post-treatment in QoL Physical and QoL Psychological based on a repeated-measures ANOVA of our preliminary data was 14.7 and 10.4 units, respectively. The effective SD from post-treatment to 6-month follow-up was 11.4 and 10.0 units, respectively. Based on these estimates, assuming an MCID of 6.25 units, allowing up to 5% loss to follow-up by post-treatment assessment, and testing each of the co-primary outcomes at  $p < 0.025$  two-sided, the study will have 80% power for QoL Physical and 96% power for QoL Psychological. Allowing up to 20% loss to follow-up by the 6-month assessment, the study will have 99% power to declaring non-inferiority of 3RP-NF vs. HEP-NF if the true treatment-dependent difference in maintenance of any change from baseline to post-treatment is zero.

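### Both arms are treated in small groups, but the primary model and the power calculation treat participants as independent, so the 5% error rate and the 80% power for QoL Physical are not secured if outcomes within a group are correlated

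*Protocol*

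**What the plan says.** Randomisation is by individual: "Participants will be randomized 1:1 to 3RP-NF or HLI" (Protocol, section V; the comparator is called HLI there and HEP-NF in most other places).

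Treatment is in groups. For 3RP-NF, section V, 1.1 says "Groups are small (5-7 participants/group". The HEP-NF programme "consists on 8 group sessions (each session is 90 minutes", and "The active comparison HEP-NF is conducted in the same format as the intervention condition" (section V, 1.2). No group size is given for HEP-NF. Section V, 1.2 also lists support and feedback from group members among the things the comparator is meant to control for, so the protocol treats group interaction as part of what is delivered. One therapist serves both arms: "We will use the same clinician/study therapist across the study conditions".

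The primary model (section VI, 3) is stated as "Data will be analyzed using a shared-baseline, linear mixed model with fully unstructured covariance among repeated measures". Each co-primary outcome is tested two-sided at 0.025, with an overall type 1 error of 5% claimed at post-intervention. The sensitivity analyses named there are a Wilcoxon test on change scores, participant-specific random effects and added baseline covariates.

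Section VI, 3.1 uses an SD of change, a difference of 6.25, 5% loss and the 0.025 level, and concludes that "the study will have 80% power for QoL Physical and 96% power for QoL Psychological".

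**The concern.** Members of a therapy group share sessions, discussion, peers and a facilitator for eight weeks, and each group belongs to one arm. A shared influence on their post-treatment scores would be expected to make those scores more alike than scores from different groups. Between-group variance then enters the treatment contrast directly and shrinks with the number of groups, not with the number of participants. A model with within-person covariance only does not see it. Confidence intervals would be too narrow, each co-primary test would reject too often under the null, and the power quoted for the outcome that sets the sample size would be too high for a test of correct size. The one-sided bounds used to judge durability at 6 and 12 months would be affected in the same way.

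**Working it through.** **Inputs from the protocol.** 224 enrolled and 212 at post-treatment, so 106 per arm (VI, 1). Difference 6.25; SD of change 14.7 (Physical) and 10.4 (Psychological) (VI, 3.1). Two-sided 0.025 per test, critical value 2.2414 (VI, 3). Group size 5-7 for 3RP-NF (V, 1.1), taken to hold for HEP-NF as well.

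**Assumption.** The ICC is not in the documents; 0.01 to 0.10 is used, with m = 6. At six per group, 224 participants make about 37 groups.

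**1. The plan's own figure.** Power = Φ(6.25 / (SD × √(2/106)) − 2.2414).
- Physical: 14.7 × √(2/106) = 2.019; 6.25/2.019 = 3.095; Φ(0.854) = 0.803. The stated 80% is the independent-participants figure, with nothing set aside for grouping.
- Psychological: 10.4 × √(2/106) = 1.429; 6.25/1.429 = 4.375; Φ(2.134) = 0.984. The stated 96% does not follow from the stated SD.

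**2. With grouping.** Design effect DE = 1 + (m − 1) × ICC.
- Power of a correctly sized test: Φ(6.25 / (SD × √(2·DE/106)) − 2.2414).
- Actual size of the unadjusted test: 2 × (1 − Φ(2.2414/√DE)).
- Overall bound: twice the actual size.
- Durability: the one-sided 5% level becomes 1 − Φ(1.645/√DE) if the same ICC persists to follow-up.

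| ICC | DE | Size of a 0.025 test | Overall bound | One-sided 5% becomes | Physical power | Psychological power |
|---|---|---|---|---|---|---|
| 0 | 1.00 | 0.025 | 5.0% | 5.0% | 80% | 98% |
| 0.01 | 1.05 | 0.029 | 5.7% | 5.4% | 78% | 98% |
| 0.02 | 1.10 | 0.033 | 6.5% | 5.8% | 76% | 97% |
| 0.05 | 1.25 | 0.045 | 9.0% | 7.1% | 70% | 95% |
| 0.10 | 1.50 | 0.067 | 13.4% | 9.0% | 61% | 91% |

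A simulation of an unadjusted t-test (18 groups of 6 per arm, 40,000 runs) gave sizes of 0.025, 0.032, 0.044 and 0.067 at ICC 0, 0.02, 0.05 and 0.10. At ICC 0.05, group sizes of 5 to 7 give Physical power of 72% to 68%.

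**3. Allowing for the shared-baseline model.** The 14.7 is an SD of change, whereas the planned model adjusts for baseline. From Table 1 in section I (Physical), averaging the two arms' variances:
- Baseline variance (17.76² + 21.16²)/2 = 381.6, SD 19.53.
- Post-test variance (19.00² + 22.21²)/2 = 427.1, SD 20.67.
- Implied correlation (381.6 + 427.1 − 14.7²) / (2 × 19.53 × 20.67) = 0.73.
- Residual SD 20.67 × √(1 − 0.734²) = 14.04.
- 14.04 × √(2/106) = 1.928; 6.25/1.928 = 3.241; power Φ(1.000) = 84%.
- With grouping: 82%, 80%, 74.5% and 66% at ICC 0.01, 0.02, 0.05 and 0.10. Power reaches 80% at an ICC of about 0.021.

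**4. Where Psychological drops below 96%.** DE = (4.375 / (2.2414 + 1.7507))² = 1.201, so ICC = 0.201/5 = 0.040 for m = 6 (0.050 for m = 5, 0.034 for m = 7).

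**The case against.** The strongest case against has four parts.

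*The harm is conditional and may be small.* No ICC is given. Participants are recruited and randomised as individuals, manuals are fixed and fidelity is checked, goals are patient-specific, and one therapist serves both arms. All of this points to a modest correlation, and the most serious figures come from the assumed upper end of 0.10. This stands as a limit on size, and it is why a range is shown. It does not remove the problem: sharing the therapist limits confounding of therapist with arm, but leaves the correlation within each session group.

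*The planned model has some power in hand.* This stands too. A reader might infer that any positive ICC takes QoL Physical below 80%. That is true of the change-score calculation in VI, 3.1, but not of the shared-baseline model, which on the pilot SDs absorbs an ICC up to about 0.02. This reserve does nothing for type 1 error.

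*The 96% is not shown to be wrong in this direction.* A reader might infer that both stated powers are overstated. On the stated SD of 10.4, independence gives 98.4%, so 96% survives to an ICC of about 0.04. The gap between 98.4% and 96% is not a hidden allowance for grouping either: a design effect of 1.20 would put Physical near 72%, not 80%. It is a separate point.

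*The SAP may add a group term.* It may, and the protocol does not forbid one. But the protocol itself fixes the primary covariance structure, claims 5% overall error and states the power behind N = 224. None of its named sensitivity analyses handles grouping: the Wilcoxon test also assumes independent participants, and the random effects are participant-specific.

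**Conclusion.** The point holds in conditional form. Following the protocol as written gives standard errors that are too small under any positive within-group correlation.

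Over an assumed ICC of 0.01 to 0.10 with groups of six, each nominal 0.025 test has a true size of 0.029 to 0.067, so the claimed 5% understates the risk. The two-test bound runs from 5.7% to 13.4%. It is an upper limit, and the overall error will be somewhat lower if the two outcomes are correlated, but 5% is no longer guaranteed.

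For QoL Physical, power is 78% to 61% on the stated SD, or about 82% to 66% if the shared-baseline gain implied by the pilot is realised. If grouping is simply ignored, the unadjusted test would still reject 80% to 76% of the time at the stated SD, but only by running at the inflated error rate. For QoL Psychological, no overstatement is shown below an ICC of about 0.04.

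These results rest on the assumed ICC, on HEP-NF groups being of the same size as 3RP-NF groups, and on normal quantiles. Small-sample degrees of freedom would lower the power figures a little further.

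**What to change.** 1. Record a therapy-group identifier for every participant.
2. Add to the primary model a random therapy-group effect nested in arm, acting on post-baseline visits only because groups form after the shared baseline, with small-sample degrees of freedom (for example Kenward-Roger). Cluster-robust standard errors with a small-sample correction are an alternative.
3. Use the same model for the one-sided durability bounds at 6 and 12 months.
4. Restate power in VI, 3.1 over an explicit ICC range, say whether the shared-baseline gain is counted, and state the HEP-NF group size.

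N can stay at 224 if the lower power is stated openly. For information, holding 80% for QoL Physical on the SD of 14.7 would need about 235, 246, 279 or 335 enrolled at ICC 0.01, 0.02, 0.05 or 0.10 (2 × 106 × DE / 0.95).

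The cost is one identifier, one model term and a rewritten power paragraph. The downside is slightly wider intervals and a less favourable power figure for QoL Physical. The change should be made before unblinding, since a group term added later would look post hoc.

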## VI. BIOSTATISTIC ANALYSIS

**1. Missing data:** We will assess for patterns of missing data, which are expected to be low as the study uses computer-assisted questionnaire completion (REDCap), which reduces participant non-response (see how missing data is handled below). The primary anticipated reason for missing data is attrition due to loss of follow up. Based on our preliminary studies, in particular our videoconferencing RCT, we do not anticipate loss of data at time 2 (100% observed retention). However, we do anticipate some loss of data for the 6 (82.5% observed retention) and 12 months follow up. Conservatively, we estimate up to 5% loss to follow-up by post-treatment and up to 20% loss to follow-up by 12 months. Hence, we plan to enroll 224 participants to achieve at least 212 at post-treatment and 180 at 6 and 12 months. We will use mixed-model maximum-likelihood techniques for analysis to minimize bias when lost to follow-up is missing at random conditional on the observed data. Attrition effects will be evaluated by testing whether systematic differences exist between those participants who completed the research versus those who drop out. In this way we can determine the nature of the potential bias introduced by study attrition. If attrition is higher in the 3RP-NF group, multiple imputation and sensitivity analyses assuming a range of informative loss to follow-up will be investigated. Note that in our preliminary study, drop-out was more common in the placebo arm, which if it reflects lack of efficacy would yield conservative estimates of benefit from 3RP-NF.

**2. Evaluating possible confounders:** In the preliminary analyses we will examine the equivalence of the random assignment of groups with regard to key baseline characteristics. This will involve assessment of the treatment groups on sociodemographic characteristics, psychosocial variables and homework completion. In the unlikely event that important differences at baseline occurred by change even with randomization, we will run analyses both with and without these variables as covariates to determine whether baseline differences may account for differences in outcomes.

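### Testing each co-primary outcome at a fixed 0.025 is valid but less efficient than Holm, which on the protocol's assumptions lifts QoL Physical power from 80% to about 87% at the same 5% family-wise error

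*Protocol*

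**What the plan says.** Section VI, item 3 (analyses for Specific Aim 1) names QoL Physical and QoL Psychological as co-primary at the post-intervention visit and fixes the decision rule: "With two co-primary outcomes, we will use two-sided tests at" p < 0.025, with the aim of "maintaining an overall 5% type 1 error at our primary post-intervention time point". Item 3.1 (power and sample size) uses the same level, "testing each of the co-primary outcomes at" 0.025 two-sided, and reports 80% power for QoL Physical and 96% for QoL Psychological. It does so "assuming an MCID of 6.25 units", with SDs of change from baseline to post-treatment that "based on a repeated-measures ANOVA of our preliminary data was 14.7 and 10.4 units, respectively", and "allowing up to 5% loss to follow-up by post-treatment assessment". No step-down rule or recycling of alpha is mentioned.

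The protocol does not say in words whether success needs one outcome or both. Dividing 5% between two tests makes sense only if superiority may be claimed on either outcome. If both were required, each could be tested at 0.05 without adjustment. I read the rule as allowing a claim on either.

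**The concern.** Under a fixed split, each outcome stays at 0.025 even after the other has been shown significant. The error allotted to the outcome that has already won is then unused. Holm reuses it: the smaller p-value is tested at 0.025 and, if that is significant, the larger at 0.05.

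This matters here because the two outcomes are unequally powered. QoL Physical has the larger SD and sits at 80%, with no margin. QoL Psychological is well above that, so under the planning assumptions it would usually release its share of alpha. What is at stake is about a 20% chance of missing a real effect on QoL Physical, part of which could be avoided without more participants.

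**Working it through.** **Inputs.** Effect 6.25 units on both outcomes; SDs 14.7 (Physical) and 10.4 (Psychological), from item 3.1. Post-treatment sample from item 1 of Section VI: "we plan to enroll 224 participants to achieve at least 212 at post-treatment". Allocation from Section V: "Participants will be randomized 1:1 to 3RP-NF or HLI", so 106 per arm. The correlation between the two test statistics is not given; I assume a range of 0 to 0.9.

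**Step 1: reproduce the stated power.** With λ = δ / (SD × √(2/n)), power is approximately Φ(λ − z). The critical value z is 2.241 at two-sided 0.025 and 1.960 at 0.05.

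- Physical: λ = 6.25 / (14.7 × √(2/106)) = 3.095. Power at 0.025 = Φ(0.854) = 80.3% (79.8% by noncentral t), matching the stated 80%. Power at 0.05 = 87.2%.
- Psychological: λ = 6.25 / (10.4 × √(2/106)) = 4.375. Power at 0.025 = 98.4%; at 0.05, 99.2%. The stated 96% does not follow from SD 10.4. It follows from SD 11.4 (96.0%), the value that item 3.1 gives for QoL Physical from post-treatment to 6 months. I use the printed 10.4 and show the alternative below.

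**Step 2: Holm, correlation 0, by hand.** Holm rejects Physical if its p < 0.025, or if its p lies between 0.025 and 0.05 and Psychological has p < 0.025:

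- Physical: 0.803 + (0.872 − 0.803) × 0.984 = 0.871.
- Both outcomes, fixed split: 0.803 × 0.984 = 0.790.
- Both outcomes, Holm: 0.790 + 0.069 × 0.984 + 0.803 × (0.992 − 0.984) = about 0.864.

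**Step 3: other correlations.** Simulated bivariate normal test statistics, 2 million draws per setting, correlation 0 to 0.9:

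| Power | Fixed 0.025 | Holm |
|---|---|---|
| QoL Physical | 80.3% | 87.0-87.1% |
| QoL Psychological | 98.4% | 98.4-99.0% |
| Both outcomes | 79.1-80.3% | 86.5-87.1% |
| At least one | 98.4-99.7% | the same |

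If QoL Psychological has the stated 96% instead, Holm gives 86.5-86.8% for QoL Physical, and power for both outcomes rises from 77-80% to 85-87%.

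**Step 4: dependence on the psychological effect.** QoL Physical is held at 6.25 units, with SDs as printed:

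| True psychological effect | QoL Physical power under Holm |
|---|---|
| 6.25 units (planning value) | about 87% |
| 5.57 units (pilot estimate, Section I, Study 5) | 86.6-86.9% |
| 4 units | 81.9-85.3% |
| 3.125 units | 80.5-83.6% |
| 0 | 80.3-80.6% |

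At zero effect and zero correlation the gain is 0.069 × 0.025, or about 0.2 points.

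**Step 5: type I error.** Under the global null both procedures have the same family-wise error: 4.9%, 4.6% and 3.6% at correlations 0, 0.5 and 0.9. If only Physical has an effect, the chance of a false psychological claim under Holm is 3.8-4.5%, against 2.5% under the fixed split. Both are within 5%.

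**Step 6: equivalent sample size.** For the fixed split to reach 87.1% on QoL Physical, n = 2 × (14.7/6.25)² × (2.241 + 1.131)² ≈ 126 evaluable per arm, against 106. That is 40 more evaluable participants in total.

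**The case against.** The strongest reply is that nothing here is wrong. The split does what item 3 claims, power is computed at the level at which the tests will be run, and the 80% reproduces. All of that stands. A reader might infer that type I error is poorly controlled or the trial underpowered by its own standard; the protocol supports neither.

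A second reply also stands: the step from 80% to 87% is conditional. The pilot's psychological effect of 5.57 units would preserve it, but that estimate came with P = .056, so a much smaller true effect is not excluded. A reader might infer that a third of the false-negative risk on QoL Physical (19.7% falling to about 13%) is removed whatever the truth. That holds only if the psychological effect is close to its planning value.

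Third, a reader might infer that the trial as a whole becomes more likely to succeed. Power for at least one outcome is identical under the two rules; Holm helps only with the second claim. Nor can the gain be credited against any loss from delivering treatment in groups: the protocol gives no intraclass correlation, and every figure above ignores clustering.

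Finally, Holm is not quite free. Each added rejection has p between 0.025 and 0.05, so a 97.5% interval for that outcome includes zero in exactly the cases that Holm adds. This does not undo the gain, but the plan has to address it.

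A separate analysis plan might already specify a step-down test. The protocol nevertheless fixes 0.025 for each outcome in both the decision rule and the power statement.

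**Conclusion.** The point holds as a cheap gain in efficiency, not as an error. Holm keeps the 5% family-wise bound under any correlation and never loses a rejection that the fixed split would make. On the protocol's assumptions it adds about 7 points of power for QoL Physical and about 7 points for establishing both outcomes.

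This rests on three things: superiority being claimable on either outcome, 106 evaluable per arm with the printed SDs, and a psychological effect near 6.25 units. The assumed correlation hardly matters when that effect is near the planning value. The size of the effect itself matters much more, and with none the two rules perform almost alike.

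**What to change.** In Section VI, item 3, replace the fixed-level rule with: *The two co-primary outcomes will be tested with the Holm procedure at overall two-sided 5%: the smaller p-value at 0.025 and, if significant, the larger at 0.05.*

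In item 3.1, restate power under Holm for each outcome and for both, and show how QoL Physical power depends on the psychological effect (for example at 6.25, 5.57, 3.125 and 0 units). Reconcile the 96% with the SD of 10.4 at the same time.

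Add a sentence on intervals: the Holm decision governs superiority, and the reported 97.5% intervals are conservative and may include zero when the second outcome is declared significant at 0.05.

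The cost is two sentences and a revised power paragraph, settled before any unblinded comparison. No participants or assessments are added. The one real drawback is that simple intervals do not match the Holm decision.

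### The durability rule does not require that superiority was shown first, so the protocol can declare that a benefit persists when there was none.

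*Protocol*

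**What the plan says.** Section VI.3 of the Protocol sets the primary test at the post-intervention visit: "With two co-primary outcomes, we will use two-sided tests at $p < 0.025$ to declare superiority of 3RP-NF". For the later visits it says: "Persistence of a benefit from 3RP-NF at 6 and 12 month follow-up times will be analyzed as a non-inferiority test of durability". The criterion is that non-inferiority "will be declared if the lower one-sided 95% confidence bound for a given co-primary outcome is less than 6.25 units" in favour of HEP-NF, the 6.25 units being the estimated MCID. It is applied outcome by outcome.

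Section VI.3.1 uses the same 6.25 units as the treatment effect for superiority power. With up to 20% loss by 6 months, it states "99% power to declaring non-inferiority of 3RP-NF vs. HEP-NF if the true treatment-dependent difference in maintenance of any change from baseline to post-treatment is zero".

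No sentence links the durability test to the result at post-intervention. Section VI.3 opens by saying that the analyses follow a sequence, but no condition is then given. By contrast, the mediation analysis in section VI.4.1 is explicitly conditional on 3RP-NF having shown an improvement over HEP-NF.

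**The concern.** A benefit can persist only if there was one. The non-inferiority comparison asks whether 3RP-NF loses more than 6.25 units relative to HEP-NF. If the arms never differ, nothing is lost and the criterion is met almost automatically. The state under which the 99% power is computed, zero difference in maintenance, includes the case of no effect at any visit. An analyst who follows section VI.3 literally could fail superiority on an outcome and still declare persistence of benefit on it.

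Maintenance of effects at 6 and 12 months is part of the Aim 1 hypothesis in section II, so this wording could reach the trial's conclusions.

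**Working it through.** **Inputs (Protocol)**
- Section VI.1: 224 enrolled, at least 212 at post-treatment and 180 at 6 and 12 months. With 1:1 allocation (section V) that is 106 and 90 per arm.
- Section VI.3.1: SD for baseline to post-treatment 14.7 (Physical) and 10.4 (Psychological); SD for post-treatment to 6 months 11.4 and 10.0.
- Section VI.3: margin 6.25, one-sided 95% bound (z = 1.645); superiority at two-sided 0.025 (z = 2.241, so 0.0125 in the direction of benefit).

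**Step 1. Reproduce the plan's power**

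P(rule met | true difference d in later change) = Φ((6.25 + d)/SE − 1.645), with SE = SD × √(2/90).
- Physical: SE = 11.4 × √(2/90) = 1.699. At d = 0: 6.25/1.699 − 1.645 = 2.033, Φ = 97.9%.
- Psychological: SE = 10.0 × √(2/90) = 1.491. At d = 0: 6.25/1.491 − 1.645 = 2.548, Φ = 99.5%.

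Both are close to the stated 99%. The stated figure therefore refers to the change from post-treatment to 6 months.

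**Step 2. No effect at any visit**

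Here d = 0 again, so the same 97.9% and 99.5% are the probabilities of meeting the rule when there never was a benefit. Superiority in the direction of benefit occurs in only 1.25% of such trials. Whatever the correlation between the two estimates, the rule is therefore met without superiority in at least 97.9 − 1.25 = 96.7% (Physical) and 99.5 − 1.25 = 98.2% (Psychological) of them, that is, about 97% and 98%.

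**Step 3. With the condition added**

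Under no effect, a persistence claim now also needs superiority, so its probability is at most 1.25% per outcome. For correlations from 0 to −0.6 (assumed; the Protocol gives none) it is 0.9-1.2% (Physical) and 1.1-1.25% (Psychological).

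**Step 4. Joint probability under the planned effect**

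Take a true 6.25-unit effect that is fully maintained.
- Superiority, Physical: SE = 14.7 × √(2/106) = 2.019; Φ(6.25/2.019 − 2.241) = 80.3% (the Protocol states 80%).
- Superiority, Psychological: SE = 10.4 × √(2/106) = 1.429; Φ(6.25/1.429 − 2.241) = 98.4% (the Protocol states 96%).
- Superiority and durability together at zero correlation: 0.803 × 0.979 = 78.7% (Physical); 0.984 × 0.995 = 97.8% (Psychological).
- Over assumed correlations of 0 to −0.5: 78-79% (Physical) and about 98% (Psychological).

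**Step 5. The other reading of the contrast**

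Section VI.3 names changes from baseline, whereas the power statement uses change from post-treatment. If the rule is applied to change from baseline, and SDs of 14.7 and 10.4 are assumed to hold at 6 months, a trial with no difference at 6 months meets it with probability Φ(6.25/2.191 − 1.645) = 88.6% (Physical) and Φ(6.25/1.550 − 1.645) = 99.1% (Psychological). Choosing the contrast does not supply the missing condition.

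**Step 6. The margin (secondary)**

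On the post-treatment to 6-month contrast, total loss of a true 6.25-unit benefit passes in 5% of trials per outcome, as designed. Total loss of a smaller benefit passes more often. For the pilot's Psychological effect of 5.57 units (section I, Study 5): Φ((6.25 − 5.57)/1.491 − 1.645) = 12%.

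**The case against.** The best defence is that the wording presupposes a benefit. The Protocol speaks of persistence and of maintaining benefits, names efficacy before durability, and refers to a sequence. A condition may well have been intended, and a statistical analysis plan that is not shown could state it. That is fair as to intent. But the Protocol itself fixes the test, bound, margin, declaration criterion and power, and as fixed the rule runs without the condition.

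It can also be said that if the arms never differ, non-inferiority in maintenance is true, so declaring it is not a type 1 error. That stands for the narrow statement. It does not stand for the label of persisting benefit that section VI.3 attaches to it. The planned between-arm contrasts of change from baseline at each visit would show the null result alongside, which limits the harm but does not alter the rule.

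Three stronger readings are tempting and not supported:
- **That the margin causes the problem.** It does not. The missing condition does; full loss of 6.25 units passes only 5% of the time.
- **That durability declared after a missed superiority test is always wrong.** If a 6.25-unit effect truly exists and is maintained, the declaration is correct even in the roughly 20% of trials in which Physical misses superiority.
- **That the main efficacy conclusion is at risk.** Section II makes 6 and 12 months secondary time points. The superiority test, its 5% type 1 error and the sample size are untouched.

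**Conclusion.** The point holds. As written, the durability rule does not distinguish a maintained benefit from no benefit at all: with no effect at any visit it is met at 6 months in 97.9% (Physical) and 99.5% (Psychological) of trials, nearly always without superiority.

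These two figures rest only on the Protocol's SDs, 90 per arm and a normal approximation. The joint figures also need a correlation that the Protocol does not give, but they barely move over the range tried. The Psychological joint figure uses the recomputed 98.4% superiority power; with the stated 96% it would be about 0.96 × 0.995 = 95.5% at zero correlation. No SD is given for 12 months, so nothing is quantified there.

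The margin deserves only a caution: because it equals the planned effect, meeting it does not exclude loss of the whole of a benefit smaller than 6.25 units.

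**What to change.** In section VI.3, add that durability is tested and claimed for a co-primary outcome only if that outcome met superiority at post-intervention. Report a met rule as a loss relative to HEP-NF smaller than 6.25 units, next to the between-arm contrast of change from baseline at the same visit, which is already planned.

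In section VI.3.1, state that the 99% assumes zero difference in maintenance and is conditional on a benefit having been shown. Add the joint probability of superiority and 6-month durability, with its assumptions: about 78-79% for Physical and about 98% for Psychological.

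This changes wording only and needs no further participants, visits or data. The price is a less favourable durability figure, chiefly for Physical. The change should be made before unblinded results are seen, since a condition added afterwards would be post hoc.
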